**Methods/design:**

Patients undergoing major abdominal surgery will be allocated into groups: postoperative non-septic patients in an emergency surgical ward (group C) and postoperative septic patients in an intensive care unit (group S). The latter will be randomized to receive CT alone (S1) or with HCT (S2). Healthy volunteers (group H) will be recruited at University Hospital Foggia.

Peripheral blood (PB) samples will be collected preoperatively (T0), at 24 h (T1), 72 h (T2), 7 (T3), and 10 (T4) postoperative days in groups S and C, and at T0 in group H. The CD34/133 cells and HIF-1 counts will be determined by flow cytometer analysis. The concentration of SDF-1a in plasma will be calculated by enzyme-linked immunosorbent assay analysis (ELISA).

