### Aims of the study

Primary objective: To determine the time course of the levels of circulating EPCs (CD133/CD34), SDF-1a, and HIF-1 in septic patients undergoing major abdominal surgery.

Secondary objective 1: To investigate the relationship between CD133/CD34, HIF-1, and SDF-1a.

Secondary objective 2: To investigate the relationship between CD133/CD34, HIF-1, SDF-1a, and the outcome of sepsis and septic shock patients treated with standard conventional therapy alone (CT) or with the addition of extracorporeal hemoperfusion therapy (HCT).

In this trial, we hypothesize that levels of CD133/CD34, HIF-1, and SDF-1a will increase in septic surgical patients as a consequence of impaired tissue perfusion and cellular hypoxia. Our hypothesis is that the stimulation of hypoxia-related factors, like SDF-1a and HIF-1, could be the primary step in the stimulation of BM stem cells. Furthermore, we assume that surviving septic patients will show higher levels of EPCs, HIF-1, and SDF-1a.

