### Flow cytometry

The samples of whole blood (100 μl) will be stained within 1 h from taking the blood sample. To analyze the viability of the cells, they will be stained with 7-aminoactinomycin D (7-AAD), which will bind to the DNA of cells that are undergoing or have undergone apoptosis (Stem Kit™ Beckman Coulter, Brea, CA, USA). The cell surface staining will be performed by adding the following fluorochrome-labeled monoclonal antibody reagents: fluorescein isothiocyanate (FITC)-conjugated anti-CD34 (Beckman Coulter, Brea, CA, USA) and phycoerythrin (PE)-conjugated anti-CD133 (Miltenyi Biotech, USA). Staining will be performed according to the manufacturer’s guidelines.

Cells will be fixed and permeabilized using the BD Intrasure kit (Becton Dickinson, Franklin Lakes, NJ, USA) and intracellular staining of HIF-1 will be performed using HIF-1 alpha (Alexa Fluor® 647 anti-human HIF-1α Antibody, BioLegend Inc., CA, USA) following the manufacturer’s instructions. The samples will be resuspended in phosphate-buffered saline and analyzed with a FACS Caliber flow cytometer (Becton Dickinson, Franklin Lakes, NJ, USA) and FCS3 software. Cell will be acquired with a four-parameter flow cytometry method (CD34 FITC/CD133 PE/CD45 PerCP/ HIF-1 ACP staining, side, and forward angle light scatter). The flow cytometer will be calibrated every 24 h and quality controls performed according to the UK National External Quality Assessment Service protocol. The number of CD34/CD133/HIF-1 cells in PB will be calculated as the count of absolute lymphocytes times the percentage (%) of gated CD34/CD133 positive cells, and expressed as absolute number of cells per 1 μl PB.

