### Enzyme-linked immunosorbent assay

The plasma concentration of SDF-1a will be calculated by the enzyme-linked immunosorbent assay kit (SDF-1a human ELISA kit, Abcam, Italy) according to the manufacturer’s instructions.

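### The HIF-1 readout is a progenitor-cell count per µl, so a HIF-1 rise and its relationship with EPC number are partly or wholly built in

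*Protocol article*

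**What the plan says.** The protocol article, under Flow cytometry, stains HIF-1 in the same tube as the surface markers: "intracellular staining of HIF-1 will be performed using HIF-1 alpha". It then defines a single quantity from that tube, a CD34/CD133/HIF-1 cell number, which is "calculated as the count of absolute lymphocytes times the percentage (%) of gated CD34/CD133 positive cells". The unit is a cell concentration in blood, since the result is "expressed as absolute number of cells per 1 μl PB". The abstract's Methods/design paragraph describes the same kind of variable: "The CD34/133 cells and HIF-1 counts will be determined by flow cytometer analysis". The article names no HIF-1 intensity, no HIF-1-positive percentage, and no HIF-1 measurement in another cell population or in plasma.

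Aims of the study treats HIF-1 as a quantity in its own right. The hypothesis is that "levels of CD133/CD34, HIF-1, and SDF-1a will increase in septic surgical patients as a consequence of impaired tissue perfusion and cellular hypoxia", and that stimulation of SDF-1a and HIF-1 "could be the primary step in the stimulation of BM stem cells". The primary objective is the time course of the three markers. Secondary objective 1 is "To investigate the relationship between CD133/CD34, HIF-1, and SDF-1a".

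SDF-1a is measured separately from any cell gate: "The plasma concentration of SDF-1a will be calculated by the enzyme-linked immunosorbent assay kit".

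**The concern.** The aims need a HIF-1 variable that can move independently of the number of progenitor cells. The variable defined is itself a number of progenitor cells. If EPCs enter the blood in larger numbers while HIF-1 expression per cell stays the same, the HIF-1 variable still goes up.

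Two results would then be hard to interpret. In the primary time course, a rise in HIF-1 could simply restate a rise in EPCs. In secondary objective 1, the HIF-1/EPC association would contain a component that is there by construction. The HIF-1/SDF-1a association would also inherit whatever association SDF-1a has with EPC number.

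There is also a point about timing. A cell has to be in the circulation before it can be counted, so HIF-1 counted only in circulating progenitors cannot show a HIF-1 signal that preceded their release.

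**Working it through.** **Inputs from the article:** the formula and unit (Flow cytometry), and the 100 µl staining volume (Blood sampling; Flow cytometry). **Assumed, because the article gives no values:** 1,500 lymphocytes per µl, 0.05% EPCs, a HIF-1-positive fraction of 0.30, and log-scale SDs of 0.3 to 0.8 for EPC count (sE) and 0.2 to 0.8 for the fraction (sH). There is no stated figure in the plan to reproduce.

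**Notation:** L = lymphocytes per µl, p = CD34/CD133-positive proportion, E = L × p = EPC count, f = HIF-1-positive fraction of EPCs, H = the HIF-1 variable.

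**Reading A, formula as written.** H = L × p = E. The two variables are identical, so r = 1.00 in any data.

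**Reading B, triple-positive count.** H = E × f.

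*Effect on the time course.* At the start E = 1,500 × 0.0005 = 0.75 per µl. Let EPCs double to 1.50.

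| | Before | After | Ratio |
|---|---|---|---|
| Reading A | 0.75 | 1.50 | 2 |
| Reading B, f stays 0.30 | 0.75 × 0.30 = 0.225 | 1.50 × 0.30 = 0.45 | 2 |
| Reading B, f falls from 0.30 to 0.15 | 0.225 | 1.50 × 0.15 = 0.225 | 1 |

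The first two rows show a twofold HIF-1 increase with no change in HIF-1 per cell. The third shows the exception: on reading B the count stays flat if the fraction falls in proportion.

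*Effect on the HIF-1/EPC relationship.* On the log scale, log H = log E + log f. If f is independent of E, the covariance of log E and log H is sE² and the variance of log H is sE² + sH², so

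r = sE / √(sE² + sH²).

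| sE | sH | r |
|---|---|---|
| 0.3 | 0.8 | 0.3 / √0.73 = 0.35 |
| 0.5 | 0.8 | 0.5 / √0.89 = 0.53 |
| 0.5 | 0.5 | 0.5 / √0.50 = 0.71 |
| 0.5 | 0.3 | 0.5 / √0.34 = 0.86 |
| 0.8 | 0.2 | 0.8 / √0.68 = 0.97 |

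A simulation with 200,000 draws per setting agreed with the formula to two decimals. Under the same assumptions the correlation of log E with log f was 0.00, so analysing the fraction removes the built-in part.

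*Effect on the HIF-1/SDF-1a relationship.* If SDF-1a has correlation ρ with log E and none with log f, its correlation with log H is ρ × sE / √(sE² + sH²). Part of the EPC/SDF-1a association is carried over and appears as a HIF-1/SDF-1a association.

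**Reading C, HIF-1-positive cells counted across the lymphocyte gate.** H = L × h, where h is the HIF-1-positive proportion of lymphocyte-gate cells. H is then not nested in E, and the correlations tabulated above do not apply. If the percentages are independent of L and of each other, the shared multiplier still gives a log-scale r of sL² / √((sL² + sp²)(sL² + sh²)). This is above zero whenever lymphocyte counts vary, but the article gives no basis for a value.

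**The case against.** The strongest reply is that the sentence is ambiguous. The slashes in CD34/CD133/HIF-1 may list separate markers, and the abstract names CD34/133 cells and HIF-1 counts side by side. On that view HIF-1-positive cells may be counted across lymphocytes (reading C), and the coupling is only the shared multiplier. This stands as a possibility, and it is why the fix starts by asking which cells are covered. It does not remove the concern, because the only percentage in the formula is that of CD34/CD133-positive cells.

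A second reply is that a journal article condenses, and a laboratory procedure may define percentage or intensity. That may be so, but this article does not leave the readout open. It states a count in the methods and again in the abstract.

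A third reply is that on reading B nothing is lost in the data, since H divided by E recovers the fraction. That is right. The fault lies in which variable is carried into the analysis and reported.

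Some stronger inferences are tempting but not supported:

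- *HIF-1 must rise whenever EPCs rise.* This is strict only on the literal formula. On reading B it fails if the fraction falls in proportion.
- *The HIF-1/EPC correlation will necessarily look strong.* An r of at least 0.71 follows only if EPC count is assumed to vary at least as much as the fraction. The article gives no SDs, and wider assumptions go down to 0.35.
- *The trial would confirm its mechanism even if none existed.* The mechanism is worded as a possibility, no objective promises proof of temporal order, and the SDF-1a/EPC comparison is independent of the HIF-1 definition.

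**Conclusion.** The concern holds as a fault in a stated definition. As written, the HIF-1 variable equals the EPC count (reading A) or is nested within it (reading B). A HIF-1 increase and the HIF-1/EPC relationship are therefore wholly built in under the first and partly built in under the second. With no link between the fraction and EPC number, the log-scale correlation is 1.00 on reading A and about 0.35 to 0.97 on reading B. The second range depends entirely on the assumed log-SDs and on independence. The existence of the coupling on reading B needs only that EPC counts vary between samples. Restoring the missing HIF-1 term to the formula moves the variable from A to B and does not cure the problem.

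One of the three primary markers is affected, and two of the three pairings in secondary objective 1. EPC and SDF-1a results, and the relationship between those two, are untouched. A count limited to circulating progenitors cannot show that HIF-1 rose before mobilisation. The change should be made, but the fault does not invalidate the study.

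**What to change.** 1. State which cells the HIF-1 count covers, and correct the formula so that it includes the HIF-1 gate.
2. Make the analysed HIF-1 variable the HIF-1-positive percentage and the median fluorescence intensity among CD34+/CD133+ cells. Use it for the time course and for the relationships with EPC count and SDF-1a.
3. Keep the HIF-1-positive cell count as a descriptive result.
4. Optionally, add as exploratory HIF-1 in the CD45-positive leukocyte gates, and an analysis relating HIF-1 and SDF-1a at one time point to EPC count at the next. The article does not say whether all events are stored, so these are possible only where the files allow. Neither would prove temporal order.

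The cost is protocol wording and re-gating of a tube that is already stained, with no new sample or reagent. Recruitment is described as ongoing, so the definition can still be changed ahead of the analysis.

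There are two downsides. Intensity must be standardised across runs, building on the 24-hourly calibration already planned. The percentage also rests on few cells: at the illustrative 0.75 EPCs per µl, 100 µl holds at most 75, and a fraction of 0.30 then has a standard error of √(0.30 × 0.70 / 75) ≈ 0.053. The number of EPC events should therefore be reported with it. The percentage and intensity remove the arithmetic coupling, but they are still measured in cells already in the blood, so the claim about order of events should stay cautious.

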### Enzyme-linked immunosorbent assay

The plasma concentration of SDF-1a will be calculated by the enzyme-linked immunosorbent assay kit (SDF-1a human ELISA kit, Abcam, Italy) according to the manufacturer’s instructions.

### Statistical analysis

The power analysis suggested that a sample size of 30 patients per group is required to detect a higher percentage of total circulating EPCs (CD133+/CD34+ cells as a percentage of all myelomonocytic cells) in septic patients vs ICU controls (assuming α = .05 and power = .95) [22]. A sample size of three patients per group is required to detect higher SDF-1 levels in the septic vs control groups (assuming α = .05 and power = .95) [10]. This number is increased to 33 per group to allow for a 20% drop-out rate.

The normality of the distribution will be assessed by the Shapiro–Wilkinson test. If the data are normally distributed, they will be expressed as mean (± standard deviation). The data will be analyzed using the repeated measurements analysis of variance. Differences between the groups at each time point will be examined post hoc using an independent sample *t* test. A paired sample *t* test will be used to detect changes within the groups. The level of statistical significance was chosen as *P* < .05. The statistical analysis will be performed with the Statistical Package for the Social Sciences (SPSS Inc., Chicago, IL) version 15.0 for Windows.

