## Background

Complicated intra-abdominal infection is a frequent cause of sepsis and septic shock in intensive care unit (ICU) patients [1, 2]. Sepsis caused by intra-abdominal infection is associated with higher mortality ranging on average 30% to 60% because of (a) the broad spectrum of infection and disease severity, (b) the crucial role of surgery in the management of intra-abdominal infection, and (c) the ongoing emergence of multidrug resistance in pathogenic organisms [3–6].

Evidence supports that the pathophysiology of sepsis moves from an initiating early/acute hyperinflammatory phase to a late/chronic hypoinflammatory and immunosuppressive phase [7]. More recently, loss of endothelial barrier integrity, inflammation, and impaired cellular oxygen have been shown to be primary contributors to sepsis-related organ dysfunction [8]. Endothelial progenitor cells (EPCs), a specific subtype of hematopoietic stem cell, are mobilized into the peripheral circulation under various pathologic conditions that are associated with vascular injury [9–14]. Mutunga et al. observed an increase of circulating endothelial cells during sepsis and concluded that endothelial damage occurs [9]. However, the quantification of EPCs in septic patients has had controversial results and Cribbs et al. demonstrated that the increased levels of EPCs were inversely associated with organ dysfunction [15]. To date, little is known regarding the relationship between EPC and organ dysfunction in septic postoperative abdominal surgical patients.

In addition, the pathway for the mobilization of EPCs from the bone marrow (BM) in sepsis or septic shock is still unknown. Emerging evidence suggests that stromal-cell-derived factor 1a (SDF-1a) mediates the migration of hematopoietic stem cells from BM to peripheral blood (PB), while hypoxia inducible factor 1 (HIF-1), which regulates SDF-1a expression, is the central mediator of the cellular response to hypoxic microenvironments [16].

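### The planned 33 patients per group cover about 9% drop-out, not the stated 20%

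*Protocol article*

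**What the plan says.** The sample size is set out in three sentences of the protocol article, Methods/design, Statistical analysis.

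- For the EPC comparison of septic patients with controls: "The power analysis suggested that a sample size of 30 patients per group is required", with the condition "assuming α = .05 and power = .95".
- For SDF-1, at the same α and power: "A sample size of three patients per group is required to detect higher SDF-1 levels in the septic vs control groups".
- For losses: "This number is increased to 33 per group to allow for a 20% drop-out rate".

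No other section gives a different drop-out rate or sample size. The effect size, standard deviation and sidedness behind the 30 are not stated. The only between-group test of means named at single time points is the independent-sample t test: "Differences between the groups at each time point will be examined post hoc using an independent sample" t test.

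**The concern.** An allowance for drop-out should leave the required number of evaluable patients once the stated proportion has been lost. Here the required number is 30 and the stated proportion is 20%, but the increase is only 3 patients on 30. If losses run at the planned rate, both the septic and the control group fall below the number that the plan says it needs for 95% power. A reader of the sample-size justification would conclude that the power is protected against 20% loss, and it is not.

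The allowance may well be used. Groups S and C are sampled up to postoperative day 10, and the Background describes sepsis from intra-abdominal infection as "associated with higher mortality ranging on average 30% to 60" per cent. That range has no time horizon and is not a drop-out rate, so it only suggests that losses in group S could be substantial.

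**Working it through.** **Inputs** (all from the Statistical analysis section): 30 evaluable per group for the EPC comparison; 3 per group for SDF-1; α = .05; power .95; drop-out 20%; 33 per group after the allowance. Equal group sizes are implied.

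**Attempt to reproduce 33**

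| Starting number | Rule | Result |
|---|---|---|
| 30 | n/(1 − 0.20) = 30/0.80 | 37.5, so 38 |
| 30 | n × (1 + 0.20) = 30 × 1.20 | 36 |
| 3 | 3/0.80 = 3.75, or 3 × 1.20 = 3.6 | 4 by either rule |
| 30 | 30 × 1.10 (a 10% addition) | 33 |
| 30 and 3 | 30 + 3 | 33 |

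Neither usual 20% rule gives 33. The figure is reached only by a 10% addition or by adding the two sample sizes together, and neither is a 20% allowance. By position, the words at the start of the drop-out sentence could refer to the SDF-1 number of three, but that reading gives 4. Only 30 makes sense as the starting point.

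**What 33 does cover**

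- Loss that still leaves 30: 1 − 30/33 = 3/33 = 9.1%.
- Remaining at 20% loss: 33 × 0.80 = 26.4, so 26 to 27 per group.
- Shortfall in enrolment: 38 − 33 = 5 per group.
- If each patient independently has a 20% chance of loss, a group of 33 keeps 30 or more only when at most 3 are lost. The binomial probability of that is about 0.08.

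**Effect on power.** The documents give no effect size, so it has to be assumed. I took a two-sample t test and solved for the standardized difference d that gives exactly 0.95 power at 30 per group, using the noncentral t distribution with 2n − 2 degrees of freedom and noncentrality d√(n/2). Power was then recomputed at smaller n.

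| Evaluable per group | Two-sided α = .05 (d = 0.947) | One-sided α = .05 (d = 0.860) |
|---|---|---|
| 30 | 0.950 | 0.950 |
| 27 | 0.927 | 0.930 |
| 26 | 0.917 | 0.921 |
| 23 | 0.881 | 0.890 |

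The row for 23 corresponds to 30% loss (33 × 0.70 = 23.1). It is a sensitivity case and not a rate that the plan states.

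The 30 may itself have been rounded up. At the extreme, where 29 per group would just have reached 0.95, power at 26 is 0.926 two-sided and 0.929 one-sided. At 20% loss the range is therefore about 0.92 to 0.93 with 26 remaining.

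**The case against.** The mismatch between 33 and 20% cannot be defended, but several points can fairly be made about its weight.

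- *The power loss is small.* From 0.95 to about 0.92 is 2 to 3 points, and the result is still high by usual standards. The primary objective is the time course of biomarkers, which such a loss would not put in doubt. This stands. The point rests on a wrong figure in the sample-size justification, not on a collapse of power.
- *The text attaches .95 to 30 per group and does not literally promise .95 after drop-out.* This is correct as a reading. Still, an allowance for drop-out has no purpose other than to preserve the required number, so the implied claim fails.
- *Published mortality is not drop-out by day 10.* This stands. A patient who dies late has already given earlier samples, and the documents do not say which time point the 30 refers to. The mortality range shows only that losses above 20% are possible in group S. Nothing in the documents suggests such losses in the non-septic group.
- *Healthy volunteers are sampled once.* This stands. The shortfall concerns groups S and C, not group H.
- *The power figures rest on an assumed test and effect.* This stands, and they are labelled accordingly. The inflation error itself uses only 30 and 20%, so it does not depend on effect size, variance or sidedness.

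**Conclusion.** The concern holds. Thirty-three per group is not a 20% allowance on 30; it covers 9.1% loss. At the stated 20% loss, about 26 septic and 26 control patients remain, against 30 required, and 5 more per group would have to be enrolled to keep 30. This conclusion follows from the article's own figures without further assumption.

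The consequence for power is modest: about 0.92 to 0.93 in place of .95. That range assumes a two-group t test whose effect gives about 95% power at 30 per group. Whether 30 is itself right cannot be checked, because the effect size and standard deviation are not given.

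**What to change.** Correct the drop-out sentence in Statistical analysis, and say explicitly that the number being increased is the 30 for the EPC comparison. Either of two forms is enough:

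1. Keep 33 per group. State that this allows for about 9% loss, and that with 20% loss (26 evaluable per group) power would be about 0.92 for the effect that gives .95 at 30. Name the test and sidedness assumed.
2. Keep the 20% allowance and the requirement of 30 evaluable, and state 38 per group (38 × 0.80 = 30.4).

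The first form costs one sentence and a slightly less favourable power statement, with no extra patients. The second costs 5 more patients in each group to which the calculation applies. Recruitment was under way when the article was written, so restating the figure is the simpler course and is sufficient.

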## Methods/design

### Recruitment

This prospective observational clinical trial is designed to target postoperative patients undergoing major abdominal surgery and healthy volunteers at University Hospital Foggia. Participants who meet pre-specified eligibility criteria (Table 1) and provide written informed consent will be enrolled in the study.

**Table 1 Tab1:** Eligibility criteria

Inclusion criteria	Exclusion criteria
Caucasian Over 18 years of age	When it is impossible to collect blood samples (organizational reasons or because of emergencies regarding the health of the patient)
	Pregnant patients
	Organ transplantation
	Palliative care
	Metastatic cancer patients

Detailed information on the benefits and risks of taking a blood sample will be provided to study candidates. Human blood samples and therapies will be acquired in accordance with institutional guidelines. All patients will be managed by applying standard protocols, following current guidelines and recommendations. The diagnosis of sepsis and septic shock will be made according to the new definitions [17].

This study is to be performed in accordance with the *World Medical Association Declaration of Helsinki: Ethical principles for medical research involving human subjects* (WMA 20 2013) [18], the *International Ethical Guidelines for Biomedical Research involving Human Subjects* (CIOMS 2002) [19], and the *ICH Harmonised Tripartite Guideline: Guideline for good clinical practice* (ICH 1996) [20].

The study has been approved by the local research ethics committee (Comitato Etico of Ospedali Riuniti, Foggia, Italy, 69/CE/2015). The trial has been registered with ClinicalTrials.gov (NCT02589535). We adhered to the SPIRIT statement (Additional file 1).

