### Study design

Each day, the anesthesiologist in the operating room and the on-call anesthesiologist will alert the principal investigator to potential eligible patients. Participants included in the trial will be divided into two groups:Group C: Postoperative non-septic patients in an emergency surgical ward (control group)Group S: Postoperative septic shock patients in an ICU

Using a computer-generated sequence of numbers, patients in group S will be randomly assigned to receive either conventional therapy for septic shock alone (CT) as per the Surviving Sepsis Campaign guidelines (S1) or standard therapy plus extracorporeal hemoperfusion therapy (HCT) with polymyxin B-immobilized polystyrene-derived fibers to remove endotoxins from the blood (S2) [21]. Healthy volunteers (group H) will be recruited from among staff members of the University Hospital Foggia (Figs. 1 and 2).

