### Blood sampling

PB samples will be collected in sterile evacuated blood collection tubes with anticoagulant ethylenediaminetetraacetic acid (EDTA; 3 ml) at the following time points:preoperatively (T0), at 24 h (T1), 72 h (T2), 7 (T3), and 10 (T4) postoperative days in groups S and CT0 in group H

The absolute numbers of leukocytes and lymphocytes in PB will be determined at the same time with an automatic cell counter (Cell-Dyn 3500, Abbott Diagnostics, Santa Clara, CA, USA). Peripheral whole blood samples (100 μl) will be used for fluorescence-activated cell sorting (FACS) analysis, and the plasma samples will be collected and stored at −80 °C.

Biochemical tests will be determined daily, according to the routine procedure in the surgical ward and ICU, and performed in the laboratories at University Hospital Foggia, according to the institutional guidelines.

Demographic, anamnestic, clinical, and laboratory data will be recorded.

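### Repeated-measures ANOVA over five samples makes the main group S time course conditional on being alive and fully sampled at day 10

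*Protocol article*

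**What the plan says.** The Statistical analysis section of the protocol article fixes the method: "The data will be analyzed using the repeated measurements analysis of variance". Two follow-on analyses are named. The first is between groups: "Differences between the groups at each time point will be examined post hoc using an independent sample" *t* test. The second is a paired *t* test for changes within groups. The section does not mention incomplete series or death before the last sample.

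Blood sampling sets five time points: "preoperatively (T0), at 24 h (T1), 72 h (T2), 7 (T3), and 10 (T4) postoperative days in groups S" and C. Group H is sampled at T0 only.

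Three other statements bear on the point:

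- Aims of the study: the primary objective is how the three markers behave over time in septic patients having major abdominal surgery. It is not restricted to survivors.
- Study design describes group S as "Postoperative septic shock patients in an ICU", and the Background says: "Sepsis caused by intra-abdominal infection is associated with higher mortality ranging on average 30% to 60" per cent.
- Aims of the study also says: "we assume that surviving septic patients will show higher levels of EPCs, HIF-1, and SDF-1a".

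**The concern.** Classical repeated-measures ANOVA needs a value at every time point. A group S patient who dies on day 5, or who misses one of the five samples, leaves the model together with the samples already taken. What remains is the course among patients alive and fully sampled at day 10, which is a different population from the one in the primary objective.

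In ICU septic shock, some deaths before day 10 must be expected. The protocol itself links survival to the marker level, so on its own premise the patients who drop out differ systematically from those who stay. At stake are the comparison of septic levels with controls, the number of patients behind the main model, and the agreement between that model and its follow-up tests.

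**Working it through.** **The plan's own figures.** The Statistical analysis section gives 30 per group at α = .05 and power .95, raised to 33 for 20% drop-out. That step does not reproduce: 30 / 0.8 = 37.5, so 38, and 30 × 1.2 = 36. The figure 33 equals 30 × 1.1, and 33 × 0.8 = 26.4, which is below 30. I use 33 below because it is the planned number. No effect size is stated. The difference implied by 30 per group is (1.960 + 1.645) × √(2/30) = 0.93 SD two-sided, or (1.645 + 1.645) × √(2/30) = 0.85 SD one-sided.

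**Assumed, not in the documents.** *m*, the share of group S lost before day 10: 15%, 30%, 60%. *δ*, the survivor minus non-survivor difference: 0.25 to 1.0 SD, plus 0 and −0.5 SD as checks. Group C is taken as complete.

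**Step 1: complete series.** 33 × (1 − *m*). Power is for a two-sided comparison with 33 controls at 0.93 SD.

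| Loss *m* | Complete series | Power | Needed per group to keep 30: 30 / (1 − *m*) |
|---|---|---|---|
| 15% | 33 × 0.85 = 28.1 | 0.95 | 36 |
| 30% | 33 × 0.70 = 23.1 | 0.93 | 43 |
| 60% | 33 × 0.40 = 13.2 | 0.82 | 75 |

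**Step 2: shift in the septic level.** The whole-group mean is (1 − *m*) × survivor mean + *m* × non-survivor mean. The survivor mean therefore exceeds it by *m* × *δ*.

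| Loss *m* | *δ* = 0.25 | *δ* = 0.5 | *δ* = 1.0 |
|---|---|---|---|
| 15% | 0.04 SD | 0.08 SD | 0.15 SD |
| 30% | 0.08 SD | 0.15 SD | 0.30 SD |
| 60% | 0.15 SD | 0.30 SD | 0.60 SD |

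With *δ* = 0 the shift is zero. With *δ* negative it changes sign.

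**Step 3: effect on the group comparison.** Simulation of 3,000 trials per setting: 33 per group, five visits, within-patient correlation 0.5 (assumed), and no true difference between the whole septic group and controls. The table gives the share of trials in which the complete-case group test wrongly finds septic above control (nominal 2.5%).

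| Loss *m* | *δ* = 0 | *δ* = 0.5 | *δ* = 1.0 | *δ* = −0.5 |
|---|---|---|---|---|
| 15% | 2.7% | 5.6% | 11.4% | 1.0% |
| 30% | 2.5% | 10.9% | 29.5% | 0.3% |
| 60% | 2.4% | 20.6% | 64.3% | 0.0% |

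**Step 4: level against trend, and the *t* tests.** All at *δ* = 0.5, constant over time, for *m* = 15%, 30%, 60%:

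- Mean change from T0 to T4 among complete cases: about 0 in every setting. The within-patient trend is not biased.
- T0 *t* test on everyone sampled: 2.2%, 2.2%, 2.5%, close to nominal.
- T4 *t* test on those still alive: 5.0%, 8.0%, 13.9%.
- T4 mean minus T0 mean, each over all patients available at that time: +0.07, +0.15, +0.29 SD. This apparent rise comes only from the changing set of patients.

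The ANOVA and its follow-up tests therefore rest on different patients and can disagree for that reason alone.

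**The case against.** The article names a method but states no complete-case rule, and a full analysis plan may deal with missing data. That is fair as regards missing-data handling in general. It does not rescue the named method, which in its classical form cannot use an incomplete series.

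Several stronger readings are tempting, and the documents do not support them:

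- *That 30% to 60% of group S will be gone by day 10.* The Background range has no time horizon, so it only bounds the loss. At an assumed 15%, 28 series remain and power is still 0.95.
- *That the result is biased towards the trial's hypothesis.* The upward direction needs survivors to have higher levels. The protocol assumes this, but its Background calls EPC findings in sepsis controversial, and its hypoxia mechanism could equally put the highest levels in the sickest patients.
- *That the time course itself is distorted.* Under a constant survivor difference, the level against controls shifts and the within-patient trend does not.
- *That every planned test is limited to survivors.* The *t* tests at early time points, and paired tests between early samples, can use everyone sampled then.
- *That most early samples are thrown away.* This holds only in the 60% scenario.
- *That Table 1 removes the sickest after enrolment.* The entry "When it is impossible to collect blood samples (organizational reasons or because of emergencies regarding the health of the patient") is listed as an eligibility criterion, not a rule for deleting enrolled patients. Likewise, group H has only a T0 sample by design and can be compared at T0.

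**Conclusion.** The point holds in limited form. The specified ANOVA answers the primary objective for group S patients who are alive and fully sampled at day 10, not for septic patients as stated. This mismatch follows from the method and the sampling schedule and needs no assumption about direction.

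The size is uncertain because the documents give neither day-10 mortality nor the survivor difference. The figures of 28, 23 or 13 complete series, and of 0.08 to 0.60 SD across 30% to 60% loss, rest on the assumed ranges above; the upper ones treat all background mortality as falling before day 10. An upward shift is conditional on the protocol's own survivor assumption and concerns the septic level against controls only.

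**What to change.** Replace repeated-measures ANOVA with a linear mixed model for groups S and C, with time as a categorical factor and a group-by-time term, fitted to every available sample. State that results are to be read as levels while alive, and show the number alive and the number sampled at each time point.

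Add one sensitivity analysis that handles death explicitly: either marker profiles by day-10 survival, or a joint model of marker level and time to death. This is a necessary part of the change, because a mixed model alone does not remove truncation by death.

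The change affects analysis wording only. It uses the same samples, and SPSS has a mixed-model procedure. The price is slightly more analysis work. The Trial status section reports that recruitment is under way, so the wording can be settled before the data are analysed.
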